#### Cost-effectiveness analysis

We will use a Markov model to perform an incremental cost-effectiveness and cost-utility analyses. The cost-effectiveness ratio is calculated by dividing the difference between the mean total costs of the intervention and control groups by the difference in mean primary clinical effects of the groups [51]. The incremental cost-utility ratio expresses the additional costs of the intervention per quality-adjusted life year (QALY) gained, compared to the usual care group.

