In the study of Mann et al. [43] 96 breast cancer survivors with problematic menopausal HF/NS were randomly assigned to either group CBT or usual care. In this study, women who had received CBT had a significantly reduced HF/NS problem rating as compared to the control group at 9 weeks and at 6 months post-randomization. Our group [44] conducted a 4-group RCT (the EVA trial) to evaluate the efficacy of group CBT, physical exercise (PE), or a combination of CBT and physical exercise in alleviating treatment-induced menopausal symptoms in breast cancer survivors, as compared to a waiting list control group (WLC) (*N* = 422). All intervention groups reported a significant decrease in levels of endocrine symptoms 12 weeks and 6 months after randomization, compared to the usual care waiting list control group. The two groups that included CBT also reported a significant decrease in HF/NS problem rating at 12 weeks and 6 months. However, in the RCT of Duijts and colleagues, noteworthy problems were observed in compliance with the group CBT. More than 50% of women attended less than 4 of the 6 CBT sessions. Many women reported scheduling conflicts related to work and child care as the reason for their under-compliance. Per-protocol analysis suggested that, if compliance rates could be increased, the intervention would be even more effective. Many women indicated an interest and willingness to undergo a CBT program administered via the Internet. This was viewed as a more flexible alternative to face-to-face group CBT, and thus is hypothesized to result in increased compliance and increased efficacy of the treatment. Further, two-thirds of breast cancer patients believe that Internet-based therapy is equally or more likely to result in improved physical and mental health, as compared to face-to-face therapy [50].

A cost-effectiveness analysis (CEA) of the EVA-trial data showed that CBT was likely to be the most cost-effective intervention, with incremental cost-utility ratios of €22,502/quality adjusted life year (QALY) for CBT versus WLC and €28,078/QALY for PE versus WLC [51]. Providing CBT via an Internet-based platform, either in a guided or self-managed format may further increase the cost-effectiveness of this intervention.

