### Current study

This randomized, controlled, multicenter trial, “EVA-Online”, is designed to evaluate the efficacy and cost-effectiveness of two Internet-based CBT programs, one guided and the other self-managed, to reduce or ameliorate treatment-induced menopausal symptoms in women who have had breast cancer. We hypothesize that women in both Internet-based CBT groups will report a significantly greater reduction in overall levels of menopausal symptoms and/or HF/NS problem rating than women in the control group. Secondarily, we hypothesize that women in both Internet-based CBT groups will report significantly greater improvement in sexual functioning, sleep quality, hot flush frequency, psychological distress and HRQOL than women in the control group. We will also evaluate the relative efficacy of self-managed versus guided Internet-based CBT, but this will be done in a more descriptive manner, given that the trial is not powered to test these differences formally. We are also investigating, in a more exploratory manner, the extent to which program compliance serves as a moderator, and hot flush beliefs and behavior as mediators of the treatment effects on the primary outcomes of interest [68]. Finally, we hypothesize that both internet-based CBT groups have a higher probability of being cost-effective compared to the control group. If demonstrated to be efficacious and cost-effective, the availability of such structured supportive intervention programs will be a welcome addition to standard medical treatment offered to cancer survivors with treatment-induced menopause.

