### Cost effectiveness

We will perform a cost-effectiveness analysis (CEA) using a validated health economic model as developed for use earlier in the EVA-trial [51]. The cost-effectiveness of the Internet-based guided CBT versus the Internet-based self-management CBT versus usual care will be expressed as: (1) cost per clinically relevant significant reduction on the problem-rating scale of the HFRS and (2) cost per QALY gained. A change of at least two points on the ten-point problem-rating scale of the HFRS, and of 0.5 SD on the FACT-ES is considered a relevant improvement [49]. A societal and hospital perspective from the Netherlands, plus a 5 year time horizon will be adopted. Future costs and effects will be discounted at 4 and 1.5%, respectively, according to the Dutch guidelines. A Markov model will be constructed with 3 mutually exclusive health states: “menopausal symptoms”, “reduction in menopausal symptoms”, and “recurrence”. Using a 6-month cycle length, the model will simulate the course of events in a hypothetical cohort of 1000 breast cancer survivors. The “effectiveness” part of the cost-effectiveness equation will be based on the HFRS (1) and SF-6D (2). The SF-6D [85], derived from the SF-36, will be mapped onto the EuroQol-5D, which will provide utilities. With the utilities, the SF-6D allows indirectly generating quality adjusted life years (QALYs) to be used in cost-effectiveness analysis.

For the direct costs, we will ask all women to report at T1 and T2 their use of health care services (e.g., GP, medical specialist, paramedical care etc.), medication use and workdays lost due to illness. In calculating the intervention costs, we will include the time spent by health professionals in providing feedback to participants (where applicable), staff training, administration, and material costs. Detailed descriptions of the intervention will be made to identify specific cost items and corresponding volumes of resource use. Subsequently, costs will be calculated by multiplying unit prices (or appropriate tariffs) by volumes of use, following the Dutch pharmacoeconomics costing guidelines [86].

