#### Modeling statistics

State of the art health economic methods will be applied. These include the estimation of the degree of uncertainty about each input parameter and the use of probabilistic sensitivity analyses. Parameter values will be drawn randomly from the assigned distributions, using Monte Carlo simulation with 10,000 iterations. The degree of uncertainty will be illustrated by using confidence intervals for costs and health effects. Scatter-plots, confidence ellipses on cost-effectiveness planes and cost-effectiveness acceptability curves will be presented [91–93]. We will use the European informal ceiling ratio of €30,000 per QALY [86]. Finally, a Budget Impact Analysis will be performed from the perspective of the health care provider.

All study results will be published in peer-reviewed publications and will result in a Ph.D. thesis. Authorship eligibility will be based on the Vancouver Protocol [94]. Participating patients will receive a lay summary of the results.

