Several limitations of the trial should also be noted. First, it would be valuable to compare the Internet-based CBT groups with a face-to-face CBT group in order to compare compliance, experience and effectiveness. However, recruitment and follow up proved to be problematic in our previous group CBT trial (EVA-study) [44]. Also we consider it important to first establish the efficacy of the Internet-based CBT program. Second, we anticipate that both intervention groups (guided and self-management) will be effective, in comparison with the control group. The trial was powered based on the estimated effects of each of the two Internet-based CBT interventions in comparison to the control group. It may also be the case that one of the two CBT programs is more or less effective than the other. One would hope, given the additional costs involved, that the guided CBT program would be more efficacious than the self-management CBT program. However, if such differences exist, the magnitude of difference will likely be smaller than that expected between the CBT programs and the control group. In order to detect a smaller difference (effect size) when comparing the two variants of the CBT program, we would need a substantially larger sample size [88]. Unfortunately, our budget, both in terms of financial resources and time, does not allow us to increase the sample size. Nevertheless, within the limits of statistical power available to us, we will calculate between CBT group differences in both efficacy and cost-effectiveness outcomes. Finally, although women in the waiting-list control group will not be provided with any materials or program elements, they might look for other options themselves. However, we do not anticipate that this will take place in a structured or systematic way. In any case, at each assessment point, women are asked to report any activities that they may have undertaken to alleviate their menopausal symptoms.

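### The cost-utility ratio is defined against usual care, while three options compete and nothing ties the guided versus self-management comparison to the €30,000 ceiling

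*Protocol article*

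**What the plan says.** Four statements in the protocol article bear on which comparator is used.

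- **Ratio definitions (Cost-effectiveness analysis).** The cost-effectiveness ratio is obtained by "dividing the difference between the mean total costs of the intervention and control groups" by the difference in clinical effect. The cost-utility ratio is the "additional costs of the intervention per quality-adjusted life year (QALY) gained, compared to the usual care group".
- **Options compared (Cost effectiveness, under the study measures).** "The cost-effectiveness of the Internet-based guided CBT versus the Internet-based self-management CBT versus usual care will be expressed as" cost per relevant reduction in problem rating and cost per QALY gained. That is three options.
- **Comparison of the two CBT versions (Discussion).** Within the limits of power, "we will calculate between CBT group differences in both efficacy and cost-effectiveness outcomes". No ratio or decision rule is attached to this.
- **Ceiling (Modeling statistics).** "We will use the European informal ceiling ratio of €30,000 per QALY". The text does not say which ratio is held against it.

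The hypothesis in Current study is that "both internet-based CBT groups have a higher probability of being cost-effective compared to the control group".

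**The concern.** Guided and self-management CBT are two ways of delivering the same program, so a provider would choose one of them, or neither, for a given woman. With options that exclude each other, the ratio that informs the choice is the one against the next less costly option still in contention. A ratio against usual care credits guided CBT with benefit that self-management could already buy for less.

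The article's own description makes this relevant. Guidance adds a telephone interview and weekly therapist feedback, and professional time counts as an intervention cost. The Discussion says: "One would hope, given the additional costs involved, that the guided CBT program would be more efficacious than the self-management CBT program". It also expects any difference between the two versions to be smaller than the difference between CBT and control. An added cost with a modest added benefit is where a ratio against usual care can mislead.

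At stake is whether therapist guidance is worth paying for. The only cost-per-QALY ratio the article defines does not answer that, yet it is the one available to set against €30,000.

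**Working it through.** The article reports no cost or QALY figure for this trial, so there is no stated result to reproduce. What can be checked is how far the two ratios can diverge.

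**Inputs**
- Ceiling L = €30,000/QALY (Modeling statistics).
- R, guided versus usual care. No figure is given for this trial. For illustration I use the Background's result from the earlier group-CBT trial: "incremental cost-utility ratios of €22,502/quality adjusted life year (QALY) for CBT versus WLC", so R = €22,502.
- c, self-management's share of guided's added cost over usual care: assumed.
- f, self-management's share of guided's QALY gain over usual care: assumed.

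**Formulas.** If guided adds cost C and QALYs E over usual care, then R = C/E and self-management adds cC and fE. Hence:
- guided versus self-management = (C − cC)/(E − fE) = R(1 − c)/(1 − f);
- self-management versus usual care = Rc/f;
- guided versus self-management exceeds L when c < 1 − (L/R)(1 − f).

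**Results, R = €22,502**

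| f | Guided vs self-management at c = 0.5 (€/QALY) | Against €30,000 | Fails for any c below |
|---|---|---|---|
| 0.5 | 22,502 × 0.5/0.5 = 22,502 | passes | 0.33 |
| 0.6 | 22,502 × 0.5/0.4 = 28,128 | passes | 0.47 |
| 0.7 | 22,502 × 0.5/0.3 = 37,503 | fails | 0.60 |
| 0.8 | 22,502 × 0.5/0.2 = 56,255 | fails | 0.73 |
| 0.9 | 22,502 × 0.5/0.1 = 112,510 | fails | 0.87 |

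In every row guided shows the same €22,502 against usual care and passes. If f = 1 and c < 1, guided costs more for no extra QALYs and is dominated, yet still shows €22,502.

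The opposite case also exists. If c > f, self-management has the higher ratio against usual care and is extendedly dominated. It drops out, and the ratio of guided against usual care is then the right one. The problem is therefore confined to c < f, and a reversal to c below the last column.

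**The same point in absolute terms (assumed values).** Over usual care, let self-management add €200 and 0.015 QALY, and guided €450 and 0.020 QALY.
- Self-management versus usual care: 200/0.015 = €13,333/QALY.
- Guided versus usual care: 450/0.020 = €22,500/QALY, under the ceiling.
- Guided versus self-management: (450 − 200)/(0.020 − 0.015) = 250/0.005 = €50,000/QALY, over the ceiling.
- Net benefit at €30,000: self-management 30,000 × 0.015 − 200 = €250; guided 30,000 × 0.020 − 450 = €150.

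Both versions pass against usual care, but self-management has the higher net benefit.

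**The case against.** The strongest reply is that the plan does not confine itself to usual care. The three-way comparison is announced in cost per QALY, and the Discussion commits to between-CBT differences in cost-effectiveness outcomes. The definitions in the Cost-effectiveness analysis section are short, written for a single intervention, and exclude nothing. Modeling statistics promises current health-economic methods and acceptability curves without saying that these are pairwise against usual care. The article condenses a fuller protocol, and rules on dominance and curve construction are the kind of detail it may leave there. Finally, the comparison between the two versions is declared descriptive and underpowered.

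Much of this stands. A reader might infer that guided is never compared with self-management economically; the text does not support that. Nor does the absence of a formula for that comparison count as a fault in a condensed article. The hypothesis against control is consistent with how the trial was powered and is not an error.

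What remains is a stated definition that is narrower than the stated question. The article does name a comparator for its ratios, and that comparator does not fit a choice among three options. Low power does not excuse this: the planned probabilistic analysis expresses decision uncertainty without a significance test.

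**Conclusion.** The point holds as a mismatch between sections. The ratios are defined against control or usual care; the question posed has three options; and the promised between-CBT comparison is not connected to the ceiling. Followed as written, the analysis could present guided CBT as acceptable value when its extra cost over self-management exceeds €30,000 per QALY gained.

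A reader might go further and conclude that the adoption decision will reverse in this trial. The documents do not support that. Costs and QALYs by arm are unknown, R is borrowed from a different, group-delivered program, and c and f are assumptions. At c = 0.5, guided passes against self-management for f of 0.5 or 0.6 and fails for f of 0.7 or more in the table. This is a worthwhile and cheap improvement, not a flaw that invalidates the economic evaluation.

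**What to change.** In the Cost-effectiveness analysis section, bring the ratio into line with the three-way comparison and the Discussion:

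1. Order usual care, self-management and guided CBT by mean cost.
2. Remove dominated and extendedly dominated options.
3. Take each ratio against the next remaining option.
4. Apply €30,000/QALY to those ratios, or equivalently compare net benefit across all three, with one acceptability curve per strategy from a single joint analysis.

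Keep the ratios against usual care as supplementary results. The hypothesis in Current study can stay as it is.

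The cost is a change of wording: the same Markov model and the same 10,000 iterations supply everything needed, with no new data. There are two downsides. Guided CBT may look less favourable than it does against usual care alone. The ratio between the two CBT versions will also be imprecise, which the probabilistic analysis will show.

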#### Modeling statistics

State of the art health economic methods will be applied. These include the estimation of the degree of uncertainty about each input parameter and the use of probabilistic sensitivity analyses. Parameter values will be drawn randomly from the assigned distributions, using Monte Carlo simulation with 10,000 iterations. The degree of uncertainty will be illustrated by using confidence intervals for costs and health effects. Scatter-plots, confidence ellipses on cost-effectiveness planes and cost-effectiveness acceptability curves will be presented [91–93]. We will use the European informal ceiling ratio of €30,000 per QALY [86]. Finally, a Budget Impact Analysis will be performed from the perspective of the health care provider.

All study results will be published in peer-reviewed publications and will result in a Ph.D. thesis. Authorship eligibility will be based on the Vancouver Protocol [94]. Participating patients will receive a lay summary of the results.

## Discussion

A relatively large percentage of young breast cancer survivors experience treatment-induced menopausal symptoms, with hot flushes being the most common and severe symptom [9, 11–14]. There is a need for effective and safe non-medical treatment options for these symptoms. Studies show that, both in the general population and among breast cancer survivors, CBT is an effective treatment method for alleviating menopausal symptoms when provided in a group setting or through guided self-help [42–44, 49]. However, compliance can be problematic [44]. A promising approach is to make this form of CBT more accessible and feasible for participants by administering it via the Internet. In the current trial we are evaluating the efficacy and cost-effectiveness of Internet-based CBT in alleviating or reducing menopausal symptoms and HF/NS problem ratings in younger breast cancer survivors who experience treatment-induced menopause. Secondary outcomes include sexual functioning, sleep quality HF/NS frequency, psychological distress and overall HRQOL.

This trial has several notable strengths, including: (1) the randomized trial design; (2) the multicenter nature of the trial; (3) the comparison of both intervention groups with a waiting- list control group; (4) the use of intention-to-treat analysis; (5) the relatively long-term follow-up; and (6) the inclusion of a cost-effectiveness evaluation.

Several limitations of the trial should also be noted. First, it would be valuable to compare the Internet-based CBT groups with a face-to-face CBT group in order to compare compliance, experience and effectiveness. However, recruitment and follow up proved to be problematic in our previous group CBT trial (EVA-study) [44]. Also we consider it important to first establish the efficacy of the Internet-based CBT program. Second, we anticipate that both intervention groups (guided and self-management) will be effective, in comparison with the control group. The trial was powered based on the estimated effects of each of the two Internet-based CBT interventions in comparison to the control group. It may also be the case that one of the two CBT programs is more or less effective than the other. One would hope, given the additional costs involved, that the guided CBT program would be more efficacious than the self-management CBT program. However, if such differences exist, the magnitude of difference will likely be smaller than that expected between the CBT programs and the control group. In order to detect a smaller difference (effect size) when comparing the two variants of the CBT program, we would need a substantially larger sample size [88]. Unfortunately, our budget, both in terms of financial resources and time, does not allow us to increase the sample size. Nevertheless, within the limits of statistical power available to us, we will calculate between CBT group differences in both efficacy and cost-effectiveness outcomes. Finally, although women in the waiting-list control group will not be provided with any materials or program elements, they might look for other options themselves. However, we do not anticipate that this will take place in a structured or systematic way. In any case, at each assessment point, women are asked to report any activities that they may have undertaken to alleviate their menopausal symptoms.

In conclusion, given the rate and severity of treatment-induced menopausal symptoms in breast cancer survivors, there is a need for more easily accessible and efficient CBT interventions for these problems. If demonstrated to be efficacious and cost-effective, the availability of such a structured supportive intervention program will be a welcome addition to standard medical treatment offered to breast cancer survivors. It is anticipated that such a program will have direct benefit in terms of symptom relief and the improvement of patients’ HRQL, while making more efficient use of health care resources.

## Abbreviations

ANOVA: Analysis of variance
CBT: Cognitive behavioral therapy
CEA: Cost-effectiveness analysis
ES: Effect size
EuroQol-5D: EuroQol 5 dimension
FACT-ES: Functional assessment of cancer therapy-endocrine symptom scale
GSQS: Groningen sleep quality score
HADS: Hospital anxiety and depression scale
HF/NS: Hot flushes/night sweats
HFRS: Hot flush rating scale
HRQOL: Health related quality of life
HRT: Hormone replacement therapy
IRB: Institutional review board
ITT: Intention to treat
MOS-SS: Medical outcome study social support scale
PE: Physical exercise
PP: Per-protocol
QALY: Quality adjusted life year
RCT: Randomized controlled trial
REML: Restricted maximum likelihood
SAQ: Sexual activity questionnaire
SD: Standard deviation
SF-36: Short form 36
SF-6D: Short form 6 dimension
SSRI’s: Selective serotonin reuptake inhibitors
WLC: Waiting list control
